## Procedures/surgical interventions

- Home hospital employs the same standard procedures used during the usual care of hospitalized patients. For example, peripheral venipuncture. Need for surgery is an exclusion criterion.

## Data to be collected and when the data is to be collected

### Cost

| Measure                                     | Source(s)                | Day(s) Obtained |
|---------------------------------------------|--------------------------|-----------------|
| Total cost, acute care episode              | Home hospital accounting | Discharge       |
| Total cost, 30-days post discharge          | Partners data            | +30             |
| Total cost, acute care episode plus 30-days | As above                 | +30             |

### Health Care Utilization

| Measure                                                | Source                                                       | Day(s) Obtained |
|--------------------------------------------------------|--------------------------------------------------------------|-----------------|
| Length of stay, days                                   | RA via MD/RN for home patients; RA EHR review for inpatients | Discharge       |
| IV medication, days                                    | As above.                                                    | Daily           |
| Intravenous fluids, days                               | RA via EHR                                                   | Daily           |
| Intravenous diuretics, days                            | RA via EHR                                                   | Daily           |
| Intravenous antibiotics, days                          | RA via EHR                                                   | Daily           |
| Oxygen requirement, days                               | RA via RN                                                    | Daily           |
| Nebulizer treatment, days                              | RA via EHR                                                   | Daily           |
| Imaging, #                                             | As above. +30 will be cross-checked with Partners data.      | Daily, +30      |
| Lab Orders, #                                          | As above.                                                    | Daily, +30      |
| MD sessions, # of notes                                | As above.                                                    | Daily, +30      |
| Consultant sessions, # of notes                        | As above.                                                    | Daily, +30      |
| PT/OT sessions, # of notes                             | As above.                                                    | Daily, +30      |
| Disposition (routine, SNF, home health, other)         | RA via MD/RN for home patients; RA EHR review for inpatients | Discharge       |
| PCP follow-up within 14 days, y/n                      | RA via pt phone call, cross-checked with Partners data.      | +30             |
| SNF utilization, days                                  | As above.                                                    | +30             |
| Home health utilization, days                          | As above.                                                    | +30             |
| All-cause readmission(s) after index, # and y/n + date | As above.                                                    | +30             |
| Unplanned readmission(s) after index, # and y/n + date | As above.                                                    | +30             |
| ED observation stay(s), # and y/n + date               | As above.                                                    | +30             |
| ED visit(s), # and y/n + date                          | As above.                                                    | +30             |

RA: Research assistant

### Safety

| Measure | Source                                                       | Day(s) Obtained |
|---------|--------------------------------------------------------------|-----------------|
| Fall    | RA via MD/RN for home patients; MD EHR review for inpatients | Daily           |

|                                        |                                                                                                                                                                                 |           |
|----------------------------------------|---------------------------------------------------------------------------------------------------------------------------------------------------------------------------------|-----------|
| Delirium, y/n and time to resolution   | RNs in home and inpatient settings calculate the CAM (standard of care in both). RA will obtain the home patient CAM via the home RN; RA will obtain the inpatient CAM via EHR. | Daily     |
| Potentially preventable VTE            | RA via MD/RN for home patients; MD EHR review for inpatients                                                                                                                    | Daily     |
| New pressure ulcer                     | As above.                                                                                                                                                                       | Daily     |
| Thrombophlebitis at peripheral IV site | As above.                                                                                                                                                                       | Daily     |
| Hospital Acquired Condition     |                                                                                                                                                                                 |           |
| CAUTI                                  | As above.                                                                                                                                                                       | Daily     |
| Clostridium difficile                  | As above.                                                                                                                                                                       | Daily     |
| MRSA                                   | As above.                                                                                                                                                                       | Daily     |
| Transfer back to hospital a | RA via MD/RN                                                                                                                                                                    | Discharge |
| All-cause mortality during admission   | RA via MD/RN for home patients; MD EHR review for inpatients                                                                                                                    | Discharge |
| Unplanned mortality during admission   | RA via MD/RN for home patients; MD EHR review for inpatients                                                                                                                    | Discharge |
| All-cause 30-day mortality             | RA via pt/caregiver call                                                                                                                                                        | +30       |
| Unplanned 30-day mortality             | RA via pt/caregiver call                                                                                                                                                        | +30       |
| Heart Failure                   |                                                                                                                                                                                 |           |
| New arrhythmia                         | RA via MD/RN for home patients; MD EHR review for inpatients                                                                                                                    | Daily     |
| Hypokalemia                            | As above.                                                                                                                                                                       | Daily     |
| Acute kidney injury                    | As above.                                                                                                                                                                       | Daily     |

a: intervention arm only

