Documentation by RN, paramedic, and MD will occur via the hospital's electronic health record. Clinical photos and flowsheets that cannot be stored in the EHR will be compiled in a Partners encrypted share drive.

Additional personnel descriptions from those listed in the Figure:

- Community health worker (CHW): a trained and certified lay person who often shares culture and/or community with the patient. The CHW strives to improve familiarity with the plan of care, improve adherence to the plan of care (medications, appointments), improve clinical outcomes, and help the patient manage social barriers to care (e.g., applying for medication financial assistance). The CHW will make once daily visits during the admission and twice weekly visits after discharge for 30 days. The CHW will have no role in providing medical decision-making or in nursing care.
- Community paramedic: a paramedic will provide in-home clinical care under the supervision of the home hospital attending. The paramedic can give medications under the direction of the attending. This paramedic will receive additional training from a collaborative group of emergency and internal medicine physicians at Brigham who have experience in community paramedicine. Our experience to-date with our paramedic has been highly beneficial to our team and patients. The paramedic will receive quality-assurance as per standard EMS guidelines.
- Medical resident: a BWH PGY2 or PGY3 in internal medicine will have the option to select home hospital service as a two-week elective. They will attend a home hospital training and continue to have twice-weekly home-based medicine seminars throughout. Their role includes daily rounds for supervised medical decision-making, responses to patient needs, and documentation. They will always have to travel with another team member when visiting a

patient's home. The home hospital attending will supervise the resident through direct observation and making addendums to documentation.

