### Study endpoints

| Study                                 | Type                                                                         | Primary                    | Secondary                                                                                                         |
|---------------------------------------|------------------------------------------------------------------------------|----------------------------|-------------------------------------------------------------------------------------------------------------------|
| Home hospital vs traditional hospital | Prospective intervention group, retrospective propensity-weighted evaluation | Cost of acute care episode | Cost of acute care episode and 30 days post-discharge
Length of stay
Unplanned readmission after index, y/n |

|                                                         |                                                                              |                                                       |                                                                                                                                   |
|---------------------------------------------------------|------------------------------------------------------------------------------|-------------------------------------------------------|-----------------------------------------------------------------------------------------------------------------------------------|
|                                                         |                                                                              |                                                       | Number of adverse events
Picker experience questionnaire                                                                       |
| Remote vs in-person home hospital physician             | RCT, non-inferiority                                                         | Number of adverse events                              | Unplanned readmission after index, y/n
Picker experience questionnaire
Global experience score                              |
| Early transfer to home hospital vs traditional hospital | Prospective intervention group, retrospective propensity-weighted evaluation | Cost of acute care episode and 30 days post-discharge | Unplanned readmission after index, y/n
Picker experience questionnaire
Global experience score
Number of adverse events* |

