## Statistical methods

### *Home hospital vs traditional hospital*

#### *Quantitative*

We plan to form 3 different control groups (with groups listed in order of preference):

1. Patients who were deemed eligible for home hospital, but the service was full (and they were not enrolled subsequently if the service was no longer full);
2. Patients who were deemed eligible for home hospital, but lived outside of the 7.5-mile catchment area; and
3. Patients who were admitted to the hospital.

For each control group, we will use propensity score weighting, adjusting for covariates of interest (see table above), baseline functional status, and DRG. We will be cognizant of over-adjustment depending on our final sample size for each group above. If possible, we will use only group 1 above, as it is the strongest. If we have insufficient control group sample size, we may choose to combine groups 1 and 2 above.

The primary outcome (hospitalization cost) will be assessed using a generalized linear model assuming a gamma distribution with a log link. We will use a multivariable regression approach for secondary

outcomes, using logistic regression for binary outcomes and non-transformed linear regression for normally distributed continuous outcomes as appropriate.

We *a priori* plan to perform a subgroup analysis that does not involve any outlier participants, should this occur. We also *a priori* plan subgroup analyses by diagnosis, by age group, by disposition, by location of admission (e.g., ED, floor, clinic, and home), and by daily activity level. We also *a priori* plan to analyze our outcomes with means, but also with median and interquartile ranges, which are less subject to outlier effects. We may choose to employ non-parametric tests of significance should our data be nonparametric.

We *a priori* plan to adjust our secondary analyses using the Benjamini-Hochberg method. We *a priori* choose a false-discovery rate of 0.20.

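### In the two home-versus-hospital comparisons, most adverse events are counted by staff report at home and by chart review in hospital, so method of counting is confounded with group

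*Protocol*

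**What the plan says.** **Sources of safety events (Safety table).** For falls, and by repetition or cross-reference for most other in-admission events, the source is "RA via MD/RN for home patients; MD EHR review for inpatients". Delirium is handled separately. Nurses score the CAM in both settings and only the retrieval differs: "RA will obtain the home patient CAM via the home RN; RA will obtain the inpatient CAM via EHR". Thirty-day mortality comes from "RA via pt/caregiver call". Transfer back to hospital carries the footnote "intervention arm only".

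**Where the count is used (Study endpoints).** Number of adverse events is a secondary endpoint of home hospital versus traditional hospital and of early transfer versus traditional hospital. For early transfer it is marked as a non-inferiority outcome. Both comparisons have the design "Prospective intervention group, retrospective propensity-weighted evaluation".

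**Controls (Statistical methods, Home hospital vs traditional hospital).** The preferred control group is "Patients who were deemed eligible for home hospital, but the service was full (and they were not enrolled subsequently". The second consists of eligible patients living beyond the 7.5-mile catchment, the third of patients admitted to the hospital. Adjustment is by propensity weighting on the listed covariates, baseline function and DRG.

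**Readmission (Health Care Utilization table).** Readmissions and ED visits come from "RA via pt phone call, cross-checked with Partners data", with no split by group.

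**Records (Study visits and measured parameters).** "Documentation by RN, paramedic, and MD will occur via the" hospital's electronic health record. Photos and flowsheets that do not fit there go to an encrypted share drive.

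**The concern.** A between-group difference in event counts can be read as an effect of care only if an event has the same chance of being counted in either group. Here the protocol fixes a different informant and a different assessor for each setting. At home, the clinicians giving the care tell a research assistant. In hospital, a physician reads the chart. Any difference in sensitivity between the two routes goes straight into the estimate.

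The bias could run either way. If chart review misses minor inpatient events such as thrombophlebitis or an early pressure ulcer, home care looks worse than it is. If unblinded home staff under-report events in their own service, home care looks better. The second case matters most for early transfer, where too few home events could produce a false non-inferiority conclusion.

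**Working it through.** **1. Sources side by side.** The Summarizing Adverse Events table has 14 items. It stands under the remote-versus-in-person analysis, but it is the only definition of the count in the document, so I take it to apply to all comparisons.

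| Items | Home | Inpatient |
|---|---|---|
| Fall, VTE, pressure ulcer, thrombophlebitis, CAUTI, C. difficile, MRSA, arrhythmia, hypokalemia, acute kidney injury, unplanned in-admission death (11 items) | treating MD/RN tells RA | physician reads EHR |
| Delirium | nurse CAM, obtained from home nurse | nurse CAM, obtained from EHR |
| Transfer back to hospital | RA via MD/RN | not collected |
| Unplanned 30-day death | patient/caregiver call | same entry; no call to non-enrolled controls described |

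The table contrasts home patients with inpatients, so I read its intervention arm as the home group.

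**2. Can the analysis repair it?** The weights use patient covariates, function and DRG. The early-transfer section adds a variable on census status. All describe the patient or the route into the study, and none describes the probability that an event is recorded.

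**3. The plan's own figure.** Power analysis, Standard Home Hospitalization: 15% vs 9% with a safety event, 641 per arm at 90% power and 493 at 80%. I assume two-sided alpha 0.05, since none is stated there.

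- n = [1.960·√(2p̄(1−p̄)) + z·√(p1(1−p1)+p2(1−p2))]² / d², with p̄ = 0.12 and d = 0.06. This gives 615 at 90% and 460 at 80%.
- With continuity correction, (n/4)·[1+√(1+4/(n·d))]², it gives 648 and 493. The second matches exactly; the first is about 1% above 641.

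**4. Illustration, percentage of patients with an event.** Capture rates are assumed. Powers use the uncorrected normal approximation at 641 per arm.

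| Capture in one group | True 15% in both: false difference | Chance it is significant | True 15% inpatient vs 9% home, inpatient events under-captured: measured difference | Power |
|---|---|---|---|---|
| 100% | 0 | 5% | 6.0 points | 91% |
| 90% | 0.15×0.10 = 1.5 points | 12% | 13.5−9 = 4.5 | 72% |
| 80% | 0.15×0.20 = 3.0 | 35% | 12−9 = 3.0 | 42% |
| 70% | 0.15×0.30 = 4.5 | 68% | 10.5−9 = 1.5 | 15% |

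If the home events are under-captured at 90, 80 or 70%, a true 6 points is measured as 6.9, 7.8 or 8.7.

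**5. Illustration, non-inferiority on counts.** Power analysis, Early Transfer, gives a baseline of 0.15 events per patient but no margin. I borrow 0.10 from the remote-versus-in-person section as an assumption. With true rates exactly at that margin (home 0.25, control 0.15), home capture of 90, 80 or 70% yields a measured difference of 0.25×0.9−0.15 = 0.075, then 0.050 and 0.025. A truly unacceptable result would look acceptable.

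**6. Transfer back to hospital.** In the appendix safety data on 203 home patients, the listed events that belong to the summary are delirium 5, thrombophlebitis 4, pressure ulcer 2 and transfer back 5, together 16. Transfer back is 5/16 of these, or 5/203 = 0.025 events per patient, on an item that controls cannot have.

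**7. Readmission.** The 528 per arm for 23% vs 15% reproduces exactly with the same corrected formula. If control readmissions were captured at 95, 90 or 80% (assumed), the measured difference would be 0.23×0.95−0.15 = 6.85 points, then 5.7 and 3.4. Power would be 82, 68 and 32%, against 91% with full capture.

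**The case against.** The strongest reply is that none of this shows a bias. Several items are laboratory results or deaths (C. difficile, MRSA, hypokalemia, acute kidney injury, in-admission death) and should hardly depend on who is asked, so one shortfall applied to every event exaggerates. If chart review is the weaker route, the error runs against home care and makes non-inferiority harder to claim. The endpoints affected are secondary; cost is primary in both comparisons. A shared source is also not automatically equally sensitive: some home material sits outside the EHR, and home charting follows a few visits a day.

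Much of this stands, and it limits the point to a risk of bias in either direction. It does not remove the confounding, which is written into the table.

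Stronger readings are tempting, but the documents do not support them:

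- *Only enrolled patients are telephoned.* The table names the call without splitting by group. The Picker questionnaire, obtained from patients at day 30, is an endpoint of the same comparisons, and interviews are planned in both arms. What can be said is that no call to non-enrolled controls is described. The Partners cross-check limits any loss to out-of-network events.
- *Delirium is measured with different instruments.* It is the nurse-scored CAM in both settings.
- *Home events are sought daily and inpatient events are not.* The daily timing applies to the whole row.

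**Conclusion.** The point holds as a confounding of counting method with group, not as a demonstrated bias. It covers 11 of the 14 summary items, plus transfer back to hospital, which one group alone can contribute. It affects a named secondary endpoint of both home-versus-hospital comparisons, and the planned weighting cannot remove it.

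A reader might infer that the safety and readmission conclusions are biased, or biased against home care. The documents give no capture rates and support neither. The sizes above are illustrations: a 10 to 30% shortfall in one group would create 1.5 to 4.5 points out of a planned 6. They assume capture acts uniformly on the percentage of patients affected. That percentage should not be mixed with the 0.15 events per patient used for early transfer.

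The readmission part is weaker. It rests on the protocol's silence about contact with non-enrolled controls. The remote-versus-in-person trial, where adverse events are primary, is unaffected because both arms are at home. The change should be made, but it does not threaten a primary endpoint.

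**What to change.** For the two home-versus-hospital comparisons only:

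- Ascertain each in-admission safety event in both groups by the same structured EHR review, with the same form and the same type of assessor. For home patients, include the flowsheets and photos held on the share drive.
- Report the adverse event count without transfer back to hospital, and show transfer back separately for the home group.
- Keep staff-reported home events as a sensitivity or descriptive analysis, and as the source for the remote-versus-in-person trial.
- Base the 30-day readmission comparison on Partners data in both groups, with phone-reported events as a sensitivity analysis. State whether controls are called. Acknowledge that out-of-network events may still be missed, especially in the control group living outside the catchment.

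The cost is protocol wording and some added chart abstraction for home patients. The protocol already takes IV fluids, diuretics, antibiotics and nebulizer days from the EHR for everyone, so a single source is workable. The downside is that events never charted drop out of the main between-group count; the sensitivity analysis shows how many there are on the home side.
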